Both the American Academy of Pediatrics and the American Society of Addiction Medicine recommend that medication be used in the treatment of young people with OUD [29–32]. Despite these recommendations, TA adults with OUD are less likely to receive MOUD than older adults [33–36]. In studies of young people with a diagnosis of OUD and covered by public and commercial insurance, one in four individuals received medications for OUD within six months of diagnosis [34, 35]. Only two randomized controlled trials of MOUD have been conducted specifically with TA adults and found that longer duration of MOUD (only 8–12 weeks in the trials) had improved outcomes over a shorter duration of MOUD [37, 38]. Studies generally find that longer retention in treatment is associated with improved outcomes [39–44], suggesting that stronger engagement in earlier treatment phases can lead to a better prognosis for TA adults [37, 38, 45–52].

Within SUD specialty treatment, MOUD increases treatment retention among TA adults [34, 53, 54]. However, TA adults generally have lower retention in specialty treatment than older adults [54, 55]. Even when MOUD is integrated into treatment, younger individuals are less adherent and more likely to leave treatment than older individuals [20, 27, 51, 56, 57]. Recent qualitative research highlights that TA adults acknowledge the life-saving potential of MOUD. Yet, they perceive receiving MOUD as stigmatizing and express ambivalence regarding MOUD, including fear of experiencing withdrawal symptoms, potential adverse effects, uncertainty regarding length of treatment, as well as concerns that MOUD might undermine self-sufficiency [58], which serves as a crucial marker of one’s transition to adulthood. There is a scarcity of studies of OUD treatment quality designed specifically for TA adults [59]. Observational studies of longitudinal cohorts are needed to identify if there are specific factors associated with use of MOUD, retention on MOUD, and adverse events related to treatment among TA adults [60].

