** *Treatment Program Organizational Characteristics* **		
Structure	Specialty opioid treatment program; program size (i.e., annual patient volume); % of TA adults among all clients; % OUD among clients; type (i.e., inpatient, outpatient); hospital system affiliation; integrated license for mental health services	OASAS Medicaid
Staffing	Number of staff; staff professionalization (e.g., degrees); gender and race/ethnicity; client-to-staff ratio	OASAS
Clinical Process	% MOUD (e.g., methadone, buprenorphine, XR naltrexone) among OUD clients; average monthly volume claims for individual, group, peer, and family counseling; average monthly volume claims for telehealth use; monthly volume for toxicology screening	Medicaid

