** *Outcome Variables* **		
MOUD Use*	Claim for methadone, buprenorphine (including formulation, e.g., sublingual tablets, sublingual film, subcutaneous injection, and implants), XR naltrexone	Medicaid
Adherence to MOUD*	Continued receipt of MOUD (continued methadone program appointments or renewal of buprenorphine or naltrexone prescriptions)	Medicaid
Retention*	Length of stay in treatment episode (in days)	Medicaid
Adverse Event*	SUD-related emergency department visit or hospitalization, including for overdose; increase in SUD level of care	Medicaid
Healthcare Utilization*	All-cause emergency department visits and hospitalizations	Medicaid

Table Notes: OASAS = CDS database; * Time-varying variables

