#### Aim 1: Quantifying associations between MOUD use and social and ecological factors

To quantify the associations between MOUD use (e.g., methadone, buprenorphine, XR naltrexone) and individual, community, and treatment program organizational characteristics, we will use generalized linear mixed effects models (GLMM). The primary outcome of interest is whether an individual received MOUD during the treatment episode. We will include random effects to account for repeated measurements within individuals and clustering by program and county, and time fixed effects to address secular trends, such as the pre- and post-COVID-19 periods. We will test whether models can be simplified by replacing time fixed effects with time-related splines or power terms. We also will explore interactions among variables of substantive interest (e.g., varying the effect of criminal justice involvement on OUD treatment by community influences and program organizational factors). We will adopt a generalized estimating equations approach with robust standard errors to ensure the robustness of our findings. To address potential bias associated with correlations between predictors and random effects, we will utilize the Mundalk approach of mean-centering variables within county. A penalization approach (lasso regression) will be used for feature selection to address overfitting and collinearity. The validity of the approach will be ensured using cross-validation and sample splitting. Given the large sample size (>65,000) across multiple years, we are powered to detect conservative odds ratios (≥1.1) with 80% power at a two-sided alpha of 0.05 (assuming 10% overall prevalence of MOUD use). Higher prevalence will lead to improved power.

*Aim 1a*: *Associations with psychological and social determinants of health*. First, we will explore the association between MOUD use and psychological and social determinants of health at both the individual (e.g., housing status, comorbid mental health diagnoses) and community levels (e.g., social vulnerability index, program availability). For each group of measures, we will build distinct GLMMs. These models will be adjusted for age, sex, race, as well as other individual baseline and time-varying covariates (as specified in the measures table).

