*Aim 1b*: *Associations with program organizational characteristics*. Second, we will focus on examining the connection between MOUD use and treatment program organizational characteristics (e.g., program size and type, volume of telehealth, integrated mental health treatment). Like Aim 1a, we will use GLMMs to analyze treatment program measures. These models will be adjusted for age, sex, race, other individual and community baseline measures, and other time-varying covariates (as detailed in the measures table). For aims 1a and 1b, estimates of odds ratios and their corresponding 95% confidence intervals will be reported.

*Aim 1c*: *Associations with MOUD options*. Third, we will investigate the factors linked to the use of different MOUD options (e.g., buprenorphine, methadone, or XR naltrexone) at individual, program, and community levels. To explore the association between medication option, provider proximity, and racial/ethnic patient characteristics, we will employ mixed effects multinomial logistic regression, while adjusting for individual, program, and county level covariates.

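### The Aim 1 primary outcome has no common observation window, so its odds ratios mix readiness to start MOUD with time in the episode before any start

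*Protocol article*

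**What the plan says.** The Aim 1 analysis section sets a binary outcome at episode level: "The primary outcome of interest is whether an individual received MOUD during the treatment episode". For the model it says "we will use generalized linear mixed effects models (GLMM", with random effects for individual, program and county, and results are reported as odds ratios. The time terms are calendar terms: "time fixed effects to address secular trends, such as the pre- and post-COVID-19 periods". Aim 1b relates the outcome to "program size and type, volume of telehealth, integrated mental health treatment", adjusting for age, sex, race and "other individual and community baseline measures, and other time-varying covariates (as detailed in the measures table". The article names no common window from admission, no person-time term and no episode-length term.

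Table 1 lists program "type (i.e., inpatient, outpatient" among the structural characteristics, and defines retention, a separate outcome, as "Length of stay in treatment episode (in days". Aim 2 then examines whether adherence and retention differ by program size, type and telehealth use, which overlap the Aim 1b exposures. Aim 2 also treats MOUD initiation as something that happens within an episode.

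**The concern.** An indicator of any receipt within the episode cannot fall as the episode lengthens, and it rises unless every start is at admission. Two programs that start MOUD equally readily will show different proportions if patients not yet on MOUD stay longer in one of them. The same holds for any patient or community characteristic linked to early departure, such as housing status or justice involvement. A program random effect does not remove this, because the length difference is tied to the exposure being estimated. Neither do calendar effects or robust standard errors.

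At stake is interpretation. The article wants its findings to inform clinical decisions and policy standards, and it presents MOUD use and retention as separate dimensions of quality. A short-stay program could appear less willing to give MOUD merely because its patients are observed for less time. A larger sample makes such a difference more likely to be declared significant.

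**Working it through.** **Inputs.** From the Aim 1 section: more than 65,000 patients, 10% overall prevalence of MOUD use, odds ratio (OR) 1.1, 80% power, two-sided alpha 0.05. Not in the article, so assumed and varied: share of patients exposed (50% to 10%), episode lengths, and share of MOUD starts on the day of admission (0% to 100%).

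**1. The plan's own figure.** OR 1.1 on 10% gives odds 0.1111 × 1.1 = 0.1222, that is 10.0% against 10.9%. With pooled variance and a 1:1 split, 80% power needs 36,986 patients in total, and 65,000 give 96.0%. With one in four exposed the power is 89.4%, with one in five 84.2%, with one in ten 59.6%. It is 80% at about 17% exposed. Ignoring clustering, the statement reproduces as at least 80% power for exposure shares of about 17% to 50%. It is not in dispute here and serves only as a yardstick.

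**2. Equal start rates, no starts on day 0.** Let h be the daily start rate, the same in both groups, and L the episode length. Then P(L) = 1 − exp(−hL). Setting P(90) = 0.10 gives P(L) = 1 − 0.9^(L/90).

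- 180 days: 1 − 0.9² = 0.190. OR = (0.190/0.810)/(0.100/0.900) = 2.11.
- 99 days (10% longer): 1 − 0.9^1.1 = 0.109. OR = 1.11.
- With 25% prevalence at 90 days, 180 days gives 43.8% and OR 2.33.

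**3. A share s of the reference group's starts on day 0.** Let p0 = s × 0.10, the same in both groups, and r = (0.10 − p0)/(1 − p0). Then P(L) = p0 + (1 − p0)[1 − (1 − r)^(L/90)]. For 180 against 90 days:

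| Share of reference-group starts on day 0 | P at 90 days | P at 180 days | OR |
|---|---|---|---|
| 0% | 10.0% | 19.0% | 2.11 |
| 25% | 10.0% | 16.9% | 1.83 |
| 50% | 10.0% | 14.7% | 1.56 |
| 75% | 10.0% | 12.4% | 1.28 |
| 90% | 10.0% | 11.0% | 1.11 |
| 100% | 10.0% | 10.0% | 1.00 |

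In the 90% row the difference would be declared significant with about 98% probability at 65,000 patients, split 1:1 and without clustering. For a stay 10% longer with 90% on day 0: p0 = 0.09, r = 0.01/0.91 = 0.0110, P(99) = 0.09 + 0.91 × (1 − 0.9890^1.1) = 0.101, OR about 1.01.

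**4. Exponential stays.** Let λ be the start rate and μ the rate of leaving among patients not yet on MOUD, with no day-0 starts. Then P = λ/(λ + μ), and the odds are λ/μ, the start rate times the mean pre-MOUD stay. Means of 90 and 180 days give 10.0% against 18.2%, OR 2.00. A mean 10% longer gives OR 1.10.

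**5. The alternatives.** With a window of W days that does not end at discharge and the same start rate throughout, both groups have P = 1 − exp(−hW), so OR = 1.00. The cause-specific hazard is λ in both groups, so its hazard ratio is 1.00. The cumulative incidence of MOUD with leaving as a competing event is again λ/(λ + μ) over full follow-up. A cumulative incidence or subdistribution comparison would therefore bring the artefact back.

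**The case against.** The strongest reply is that the analysis may be by person-month. The article says ongoing measures are assessed monthly, marks MOUD use as time-varying in Table 1, and includes random effects for repeated measurements within individuals. In such a model the outcome would not simply accumulate with stay. This stands as a partial mitigant, but the sentence that names the primary outcome is at episode level, and the monthly wording does not override it.

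A second reply is that receipt within the episode is a legitimate quality measure, since keeping patients long enough to start MOUD can be part of performance, and the article is cautious about causal claims. That also stands. It supports keeping the measure, but not as the only primary reading of MOUD use when retention has its own aim.

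A reader might infer more than the documents support:

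- **That MOUD adds to the bias by lengthening the episode.** The Introduction says: "Within SUD specialty treatment, MOUD increases treatment retention among TA adults". But once MOUD is received the outcome is already positive, and later days cannot change it. The statement shows only that adjusting for length of stay is not a clean remedy, because length of stay is partly a consequence of MOUD.
- **That the spurious odds ratio equals the ratio of mean stays.** This holds only for pre-MOUD stay, exponentially distributed, with no day-0 starts. If programs differ only in stay after MOUD starts, the artefact is nil.
- **That very large odds ratios should be expected.** Mean stays of 1 and 6 months at a start rate of 0.10 per month give 9.1% and 37.5%, OR 6.0, but nothing in the article supports those inputs.
- **That Aim 1 duplicates Aim 2.** Aim 2 models discontinuation after a start and treatment completion, which are different outcomes.

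**Conclusion.** The point holds in a limited form. Given an episode-level outcome, the direction follows from the definition: if any MOUD starts after admission, longer pre-MOUD stay raises the proportion with MOUD at an unchanged start rate. It biases a given odds ratio only where pre-MOUD stay differs by that characteristic. The article does not report such differences, though they are plausible for inpatient against outpatient programs.

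The size is unknown. At 10% prevalence, doubling a 90-day episode gives anything from 2.11 down to 1.00 as the share of day-0 starts rises from none to all. Timing of starts is thus the key unknown. The artefact can be as large as the effect the study says it can detect, but the documents do not show that it will be. This is a worthwhile, inexpensive improvement and not a fatal flaw.

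**What to change.** Define the Aim 1 primary outcome as any MOUD claim within a fixed window after admission (for example 30 days), whether or not the episode has ended, among patients enrolled in Medicaid over that window. Alternatively, analyse time to first MOUD as a cause-specific hazard, with follow-up ending at episode end and admission-day starts counted as events. Do not use a subdistribution or cumulative incidence comparison for this purpose. Keep receipt at any time in the episode as a secondary outcome, and state whether the unit of analysis is the episode or the person-month. Do not rely on adjustment for length of stay.

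The costs are modest:

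- Starts after the window count only in the secondary outcome.
- Counting MOUD from other providers loosens attribution to the index program, so report index-program MOUD alongside.
- Requiring enrolment over the window drops some patients; report how many.
- If start rates fall after discharge, the fixed-window result will still reflect stay to some degree, but as a real difference in receipt over the same period.

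The claims are already held, and the status section says that no analysis had been done, so the change can be made before results are seen.

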#### Aim 2: Evaluating program organizational factors influencing OUD treatment retention

This objective focuses on analyzing program organizational characteristics associated with improved medication adherence and retention in OUD treatment among TA adults, while controlling for individual and community characteristics related to retention in care. Employing time-to-event analysis, a set of statistical methodologies focusing on the time until an event occurs, we will focus on a) discontinuation of MOUD use following initiation during the treatment episode and b) treatment completion as our event outcome of interest. To accommodate the longitudinal structure of these data, we will employ extended Cox models. We will assess the validity of the proportional hazards (PH) assumption for time-invariant variables through log-log plots, observed versus expected plots, goodness-of-fit testing, and the use of time-dependent variables. Variables not adhering to the PH assumption will be assessed for interaction with time and, if necessary, incorporated into the final Cox model. We will assume non-informative censoring, meaning that censoring and the event risk are independent after conditioning on observable features.

These models will yield hazard ratios, critical in evaluating the hypotheses stated. To mitigate confounding, we will introduce individual, program, and community-level variables into the model, yielding adjusted hazard ratios alongside point estimates and 95% confidence intervals. The extensive confounding measures at individual, program, and community levels collectively address bias stemming from omitted or uncontrolled confounding variables. We will conduct robust sensitivity analyses and explore variation in association strength due to plausible instruments for program selection, such as patient travel distance to programs and concurrent MOUD use among other individuals in the same community. To prevent overfitting, we will apply techniques outlined in Aim 1. As a sensitivity analysis to consider the multilevel structure of the data, we will deploy extended mixed-effects Cox models. An extended Cox model can incorporate time-dependent factors [99]. A mixed-effects Cox model can incorporate multiple fixed and random effects [100]. Specifically, we will include a fixed effect for each individual, program, and community-level variable defined above and random effects for repeated measures of an individual over time, program, and community.

*Aim 2a*: *Program structural factors and adherence and retention in OUD treatment*. First, we will investigate the association between program structural factors (e.g., program size and type) and adherence and retention, guided by the hypothesis of adjusted hazard ratios being equal to 1.

*Aim 2b*: *Program staff characteristics and adherence and retention*. Second, we will examine the relationship between program staff characteristics (e.g., professional degrees) and adherence and retention, guided by the hypothesis of adjusted hazard ratios being equal to 1.

*Aim 2c*: *Clinical care process measures and adherence and retention*. Third, we will analyze the association between clinical care process measures (e.g., use of telehealth, counseling modalities) and adherence and retention, guided by the hypothesis of adjusted hazard ratios being equal to 1.

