### Study design and aims of the study

Our study introduces a retrospective, longitudinal cohort design to assess treatment quality practices and outcomes among TA patients with OUD in NYS using administrative data from 2010 through 2025. We will combine Medicaid claims and encounter data with data from the Client Data System (CDS), a state registry of treatment episodes in licensed SUD treatment programs. CDS is an Office of Addiction Services and Supports (OASAS) treatment registry that all licensed providers of SUD treatment in the state of New York use to enter admission and discharge data. Data include demographics (e.g., age, race/ethnicity, and marital status), level of functioning (e.g., housing status, health status, and comorbid mental health), criminal justice status, recent history and frequency of substance use, and recent SUD treatment history. This registry data will supplement information from the Medicaid data with additional socio-demographic and clinical information as well as SUD treatment that was not funded by Medicaid. Therefore, despite fragmentation in funding sources, the combination of these administrative data sets will yield a more inclusive record of treatment episodes. Through this targeted, innovative approach, we intend to identify the diverse treatment outcomes within this specific demographic across different program organizations and communities. The study has been reviewed by the Institutional Review Board of NYU Grossman School of Medicine (#s22-00914) and meets the criteria for exemption under 45 CFR 46.104(d). Study findings will be disseminated via national and international conferences, reports, and peer-reviewed publications.

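### Aim 2 models retention as time to treatment completion, although Table 1 defines it as length of stay; on the ordinary meaning of completion the hazard ratio does not register dropout.

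*Protocol article*

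**What the plan says.** The Aim 2 analysis section of the protocol article sets the objective as "analyzing program organizational characteristics associated with improved medication adherence and retention in OUD treatment among TA adults". It names two time-to-event outcomes. The first is "discontinuation of MOUD use following initiation during the treatment episode". The second is "b) treatment completion as our event outcome of interest".

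On the model it says "To accommodate the longitudinal structure of these data, we will employ extended Cox models", and on censoring "We will assume non-informative censoring, meaning that censoring and the event risk are independent after conditioning on observable features". Mixed-effects Cox models are a sensitivity analysis. Aims 2a to 2c then test program structure, staffing and clinical processes against "adherence and retention, guided by the hypothesis of adjusted hazard ratios being equal to 1".

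The outcome block of Table 1 defines retention differently, as "Length of stay in treatment episode (in days"), with Medicaid as the only source. Table 1 has no variable for completion, and the article does not define the term. It also does not say which direction of the hazard ratio means better retention.

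The section on study design and aims describes the state treatment registry (CDS) as one that licensed providers "use to enter admission and discharge data". It adds that the registry supplies treatment that Medicaid did not pay for.

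**The concern.** Length of stay and time to completion are different outcomes. The Introduction treats longer retention as favourable, and the Discussion names early attrition as a problem in this age group. A stay can end in two ways, by completion or by leaving beforehand. Length of stay responds to both. A Cox model with completion as its only event responds to the first, and whatever ends the stay in the second way has to be handled somehow.

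The first Aim 2 event fills part of the gap, because a patient on MOUD who leaves care and stops medication is counted there. It does not cover patients who never started MOUD, or exits that are not a MOUD stop.

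Retention is half of Aim 2 and part of one of the three quality dimensions in the abstract. If its event does not register dropout, a program feature that keeps patients in care much longer could be reported as having no association with retention. A feature that shortens stays could be reported as favourable.

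**Working it through.** Aim 2 gives no sample size, event count or hazard, so there is no figure of the plan to reproduce. The check is whether a completion hazard ratio carries information about length of stay.

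**Set-up.** Let c be the monthly hazard of completion and d the monthly hazard of leaving without completing, both constant. All values of c and d are assumptions. With dropouts censored:

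- completion hazard ratio = c1 / c0
- hazard ratio for any end of episode = (c1 + d1) / (c0 + d0)
- mean stay = 1 / (c + d)
- share completing = c / (c + d)

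The first formula does not contain d. That holds for any hazards and does not depend on the values chosen below.

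**Example.** Two programs with c = 0.10, and d = 0.05 versus 0.20:

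- completion hazard ratio = 0.10 / 0.10 = 1.00
- mean stay = 1 / 0.15 = 6.7 months versus 1 / 0.30 = 3.3 months
- share completing = 0.10 / 0.15 = 67% versus 0.10 / 0.30 = 33%
- any-exit hazard ratio = 0.30 / 0.15 = 2.00

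**Range of scenarios**, against a reference of c = 0.05 and d = 0.10:

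| Scenario | c | d | Completion HR | Any-exit HR | Mean stay (months) | Share completing |
|---|---|---|---|---|---|---|
| Reference | 0.05 | 0.10 | 1.00 | 1.00 | 6.7 | 33% |
| Dropout doubled | 0.05 | 0.20 | 1.00 | 1.67 | 4.0 | 20% |
| Dropout halved | 0.05 | 0.05 | 1.00 | 0.67 | 10.0 | 50% |
| Both hazards × 1.5 | 0.075 | 0.15 | 1.50 | 1.50 | 4.4 | 33% |
| Completion × 1.5, dropout halved | 0.075 | 0.05 | 1.50 | 0.83 | 8.0 | 60% |
| Completion × 0.7 | 0.035 | 0.10 | 0.70 | 0.90 | 7.4 | 26% |

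The completion hazard ratio stays at 1.00 while mean stay moves from 4.0 to 10.0 months. A ratio of 1.50 goes with a shorter stay in one row and a longer stay in the next. The any-exit ratio tracks mean stay in every row.

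**Simulation.** Cox models were fitted to 10,000 simulated patients per group with a 24-month cut-off and dropouts censored. The completion hazard ratio was 1.00 (95% CI 0.94 to 1.06) with dropout doubled and 1.00 (0.96 to 1.05) with dropout halved. When dropouts were kept in the risk set until the cut-off, as in a subdistribution model, the ratios became 0.58 and 1.50. The handling of dropouts, which the article does not state, therefore decides the result.

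**The case against.** **Completion is undefined, and a harmless reading exists.** Table 1 builds retention from Medicaid, while the discharge data are described as part of CDS. Completion may therefore simply mean the end of the episode. The hazard ratio would then track length of stay, with values above 1 meaning shorter stays. This stands as a possibility. The article does not say so, however, and the ordinary meaning excludes dropout. Even on this reading the event and the favourable direction need stating.

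**The article does not say that dropouts are censored.** This is correct. A reader might infer that it declares dropout non-informative, but it makes a general assumption that is conditional on observed features. Censoring of dropouts follows only by implication, from naming completion as the event and naming no competing-risk method.

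**The first event captures failure.** This also stands. It would be wrong to infer that the Aim 2 hazard ratios as a whole say nothing about patients who leave. The gap concerns the second event.

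**Completion is a legitimate outcome.** The Conceptual framework counts achieving the goals of treatment as an outcome, and Table 1 includes inpatient and outpatient programs. A single any-exit event mixes planned completion with dropout and disadvantages programs with short planned stays. This is a fair objection to any-exit as the only analysis, and the reason to report the two exits separately as well. It does not make completion a measure of length of stay.

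**A journal article condenses.** Operational definitions and censoring rules may sit in a fuller plan. Here, though, the article names both the outcome and the event, and the two do not match. That is a conflict between stated choices.

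The listed sensitivity analyses (mixed-effects models, instruments for program selection) do not answer the point, because they keep the same event.

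**Conclusion.** The point holds for the second Aim 2 event. On the ordinary meaning of completion, and with dropouts censored by implication, the retention hazard ratio does not reflect differences in dropout and has no fixed direction relative to length of stay. The absence of the dropout hazard from the ratio is a general result. The sizes (1.00 with mean stay 6.7 versus 3.3 months, or 1.50 with 4.4 or 8.0 months) rest on assumed constant hazards and serve as illustration only.

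A reader might also infer from the Medicaid-only source in Table 1 that recorded stays end when coverage or billing ends. The article does not support that as stated. Its design section says that the registry supplements Medicaid to give a fuller record of episodes. What remains is a secondary inconsistency between that section and the source cell for retention.

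**What to change.** 1. Make the retention event the end of the treatment episode for any reason, which matches length of stay, and state that a hazard ratio below 1 means better retention. If completion was already meant this way, say so and give the same direction.
2. Where discharge type is available, also report cause-specific hazards and cumulative incidence for completion and for leaving without completion as competing events. This separates planned completion from dropout, including across inpatient and outpatient programs. That CDS records discharge type is an assumption, since the article does not confirm it.
3. Keep MOUD discontinuation among initiators as the adherence event, and say that it does not stand in for retention.
4. Reconcile the Medicaid-only source for retention in Table 1 with the design section, for example by taking episode dates from CDS admission and discharge records together with Medicaid.

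The cost is a redefinition and one competing-risk analysis on data to which access has already been acquired. The status section says that no analysis had been done at the time of writing, so the change could be made before any Aim 2 result is known.
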